### Follow-Up Period

First, a WeChat group was created for parents of participants to facilitate communication and monitoring about diet and exercise recording, as well as scheduling follow-up appointments. Second, adherence to the study interventions were uniformly assessed in both groups at each visit. Third, if participants missed any visits, investigators would contact them directly by telephone to encourage continued participation and evaluate barriers.

The research assistant attempted to establish contact with the missed participants. A dropout participant was defined as someone who had not been reached for 3 months. If participants decided to withdraw before completion, all collected data would be remained for analysis.

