### Sample Size

The primary outcome was the change in body weight from baseline to 1 month. The sample size calculation was based on the difference in weight change between the 2 groups: the TAAT group and the ILCD group.

Our pilot data from 12 patients revealed a weight loss of 1.9 kg after 4 weeks of TAAT and a weight reduction of 1.4 kg after 4 weeks of ILCD, with an SD of 1.1 kg. We assumed a 0.5 kg difference in weight reduction between the 2 arms, power of 0.80, a 2-sided α of .05, and a sample size ratio of 3:1, a minimum sample size of 150 for the TAAT group and 50 for the ILCD group were required, respectively. Assuming a dropout rate of 15%, the trial enrolled at least 240 participants. The “test for 2 means module” of the PASS 16.0 software was used.

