### Data Management and Monitoring

Trained clinicians were input data onto a paper-based clinical research form designed by the research team. Once data collection was complete for each participant, it would be entered into an electronic database with built-in checks to ensure completeness. Data monitoring has occurred periodically throughout the study. We used access to create a database, and 2 investigators independently performed dual data entry twice. Once verified, the database was saved appropriately. After confirming the accuracy of the database, it was locked and submitted to an independent statistical team for analysis.

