### Statistical Analysis

Primary statistical analyses were conducted using the intention-to-treat strategy. Sensitivity analyses were performed using per-protocol set analysis.

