#### Analysis of Primary Outcome

The primary outcome in this study was the change in body weight from baseline to 1 month. A generalized linear model (GLM) was used to compare the difference in weight change between the groups, with the baseline body weight as the covariate, to obtain the estimate of the mean difference in body weight change and its 95% CI, using Gaussian for family function and identity for link function.

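### The stated per-protocol sensitivity analysis cannot show whether missing 1-month weights affect the intention-to-treat result

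*Protocol article*

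**What the plan says.** The Statistical Analysis section of the protocol article reads: "Primary statistical analyses were conducted using the intention-to-treat strategy. Sensitivity analyses were performed using per-protocol set analysis".

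For the primary outcome, the article states: "A generalized linear model (GLM) was used to compare the difference in weight change between the groups, with the baseline body weight as the covariate". The family is Gaussian with identity link, and the response is a single change value per child, from baseline to 1 month.

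On withdrawal, the Follow-Up Period section says: "If participants decided to withdraw before completion, all collected data would be remained for analysis". The same section provides for telephone contact after a missed visit and defines a dropout as a child not reached for 3 months. Table 1 schedules weight at baseline, 1 month and 3 months. The Sample Size section allows for 15% dropout and enrols at least 240 children.

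**The concern.** A child with no 1-month weight has no change value and cannot enter the model as written. The estimate therefore comes from children with an observed 1-month weight. It stands for all randomised children only if, given arm and baseline weight, those who are missing would have changed as the others did. That assumption is what a sensitivity analysis should test here.

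A per-protocol analysis does not test it. It starts from the same observed weights and then removes children who did not follow the protocol, so a child missing from the primary model is missing from the check too. The two results could agree closely while both are wrong in the same direction, and a reader would be reassured without cause.

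Unequal loss is plausible. The Discussion says that all participants come to the TCM department seeking TCM treatment. One in four is allocated a self-administered diet, while weekly follow-up is described for the TAAT arm. If children who leave lose less weight than those who stay, the arm with more missing children looks better than it should.

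**Working it through.** **Inputs from the Sample Size section.** "We assumed a 0.5 kg difference in weight reduction between the 2 arms"; "with an SD of 1.1 kg"; "power of 0.80, a 2-sided α of .05, and a sample size ratio of 3:1"; 15% dropout; at least 240 enrolled. The pilot "revealed a weight loss of 1.9 kg after 4 weeks of TAAT and a weight reduction of 1.4 kg after 4 weeks of ILCD".

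**The plan's own figure.** For a 3:1 ratio, the ILCD arm needs

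n = (1 + 1/3) × (1.960 + 0.842)² × 1.1² / 0.5² ≈ 50.7, so 51.

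That gives 51 + 153 = 204, against the stated 50 + 150 = 200. Power at 50/150 is 0.795 (normal approximation) or 0.791 (noncentral t). For dropout, 200/0.85 = 235.3, so 236, and 204/0.85 = 240. The stated 240 reproduces. The calculation is therefore built on about 204 children observed and 36 lost.

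**Precision with 153/51 observed.** SE = 1.1 × √(1/51 + 1/153) = 0.178 kg. The smallest significant difference is about 1.96 × 0.178 = 0.35 kg.

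**Effect of missing weights, common shortfall.** Let mT and mC be the fractions missing in TAAT and ILCD, and let leavers in both arms lose s kg less than stayers. If the observed difference is 0.50 kg, then

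all-randomised difference = 0.50 − (mT − mC) × s.

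The splits and s are assumptions, not figures from the article. Each split totals 15% of 240 (180 TAAT, 60 ILCD); for example, 10% of 180 + 30% of 60 = 18 + 18 = 36.

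| Missing TAAT / ILCD | s (kg) | All-randomised difference (kg) | Observed 0.50 kg is |
|---|---|---|---|
| 10% / 30% | 1.0 | 0.50 + 0.20 = 0.70 | 0.20 too low |
| 10% / 30% | 1.4 | 0.50 + 0.28 = 0.78 | 0.28 too low |
| 12% / 24% | 1.0 | 0.50 + 0.12 = 0.62 | 0.12 too low |
| 12% / 24% | 1.4 | 0.50 + 0.17 = 0.67 | 0.17 too low |
| 15% / 15% | any | 0.50 | unbiased |
| 20% / 0% | 1.0 | 0.50 − 0.20 = 0.30 | 0.20 too high |

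**Alternative: missing children lost nothing.** Here the shortfall is 1.9 kg in TAAT and 1.4 kg in ILCD, and the all-randomised difference is (1 − mT) × 1.9 − (1 − mC) × 1.4:

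- 15% / 15%: 1.615 − 1.190 = 0.425 kg
- 20% / 0%: 1.52 − 1.40 = 0.12 kg
- 10% / 30%: 1.71 − 0.98 = 0.73 kg

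Equal loss is therefore harmless only if the shortfall is also the same in both arms.

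**Shift in one arm only.** With 15% missing in each arm and only the TAAT leavers doing worse, the difference falls to the 0.35 kg threshold at s = (0.50 − 0.349)/0.15 ≈ 1.0 kg. This is why shifts should be set separately by arm.

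The per-protocol set contains none of the missing children in any row, so it can distinguish none of these scenarios from another.

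**The case against.** The strongest reply is that an article condenses a fuller protocol, and that missing-data methods usually sit in an SAP that is not shown. That stands: the absence of an imputation rule is not the point, and it cannot be said that nothing tests the result. The article is not silent on sensitivity analysis, however. It names one, and the one named does not address missing outcomes.

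The magnitudes are also assumed. The article gives no split of losses by arm and no timing. Because dropout means unreached for 3 months, the 15% is not a forecast of missing 1-month weights, which could be fewer or more. And if ILCD loses more children, the bias works against TAAT and is conservative for a superiority claim. All of this stands and limits the point to a check worth having.

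Three stronger readings are tempting, and the text does not support them:

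- A reader might infer that only children who complete the study are analysed. A child who leaves after month 1 has the primary outcome and is included.
- A reader might infer that measurement ends at withdrawal. The sentence on withdrawal retains data, which fits intention-to-treat. It does not say that weighing stops, and telephone contact follows missed visits.
- A reader might infer from Data Management and Monitoring ("Once data collection was complete for each participant, it would be entered into an electronic database") that withdrawn children are never entered. That sentence describes workflow. Collection can be complete for a child who has left, nothing limits entry to finishers, and periodic data monitoring is mentioned.

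**Conclusion.** The point holds in narrow form. The primary model as written uses children with an observed 1-month weight, and the named sensitivity analysis uses a subset of them, so it cannot show whether the planned-for losses change the result.

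If the full 15% lacks a 1-month weight, split 10% TAAT and 30% ILCD, and leavers lose 1.0 kg less, the error is 0.20 kg. That is 40% of the 0.5 kg target and a little more than one standard error, and it understates TAAT's advantage. A split weighted towards TAAT reverses the sign: at 20% / 0% and the same shortfall, an observed 0.50 kg corresponds to 0.30 kg, below the roughly 0.35 kg needed for significance. Equal loss with a common shortfall gives no bias. These sizes rest on assumed splits and shortfalls. They show that the conclusion could change, not that it will.

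**What to change.** **Statistical Analysis.** Keep per-protocol as a supplementary analysis. Make the sensitivity analysis for the primary outcome one that includes every randomised child. An example is multiple imputation by arm, with the missing children's weight loss shifted in steps from 0 to 1.4 kg less, separately by arm, reporting the shifts at which the conclusion changes. The upper step corresponds to no loss at all at the ILCD pilot mean. The shift does the testing: imputation from arm and baseline weight alone would largely return the primary estimate.

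**Follow-Up Period.** Add that children who stop the assigned treatment but do not withdraw consent are still invited to the existing 1- and 3-month weighings, and that those weights are used in the primary analysis.

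**Cost.** A little more analysis work, a wider interval in the sensitivity analysis and a few reminder calls. The visits and scales already exist. The wording should be fixed before the database is locked and handed to the statistical team.

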### Outcomes

#### Primary Outcome

Change in body weight from the beginning of the treatment to 1 month.

#### Secondary Outcomes

Secondary outcomes included body weight, waist circumference, waist-to-height ratio, BMI, blood pressure (BP), body fat content, glucose metabolism, blood lipid levels, liver and kidney function, composition of gut microbiota, and TCM syndrome score, and were assessed at the end of 1 month and 3 months, respectively.

### Measurement

#### Anthropometry

Including the measurements of weight, height, waist circumference (WC), and BP. These measurements should be taken by the same person, using the same instruments, at the same time of day. Each measurement should be taken 3 times in a row, and the average of the 3 values should be used.

(1) **Weight measurement:** The participant should be weighed in light clothing and preferably with an empty bladder. They should also remove shoes, heavy jewelry, and watches. The electronic weight scale should display 0.0 before the participant stands on it. The participants should stand with their feet together in the center and their heels against the back edge of the scales. The participant’s arms should be hanging loosely at their sides and their head should be facing forward. The weight measurements were recorded in kilograms and were accurate to 0.1.

(2) **Height measurement:** Height should be measured using a stadiometer with the participant standing barefoot and with feet together. The head should be positioned level with a horizontal Frankfurt plane, which is an imaginary line from the lower border of the eye orbit to the auditory meatus. Any hair knots or braids that may interfere with the measurement should be untangled. The press plate should be in contact with the head with moderate tightness. The height measurements were recorded in centimeters with an accuracy of 0.1.

BMI was a widely used tool for assessing the risk of overweight and obesity in individuals. It was calculated using the following equation:

(3) **Waist circumference measurement:** The measurement should be taken while the participant exhales. WC was measured by placing a tape measure around the waist, 1 cm below the navel, with the participant standing and arms naturally at their sides. Record the data in centimeters with an accuracy of 0.1.

Waist-to-height ratio had emerged as a surrogate for abdominal obesity that also takes into account body size and allows the same cut of across age and gender [25]. It was calculated using the following equation:

(4) **Blood pressure measurement:** BP was measured on the right arm using the CONTEC08A electronic sphygmomanometer (CONTEC Medical Systems Co). The participant should be seated in a quiet room for 3-5 minutes before measurement, with the back supported and feet uncrossed on the floor. The right arm should be at heart level, supported, and uncovered above the cuff. The correct cuff size should be used. The bladder length should be 80%-100% of the circumference of the arm, and the width should be at least 40%.

#### Body Fat Content

Body composition was measured by determining the body fat percentage using the LUNAR dual photon X-ray dual-energy X-ray absorptiometry equipment (General Electric Company). Dual-energy X-ray absorptiometry was a medical imaging technology that used low dose radiation for a whole-body scan to provide accurate measurements of fat percentage. The equipment was operated by qualified professionals.

#### Venous Blood Tests

The tests were conducted after a 10-hour overnight fast to avoid any influence of diet on the test results. The tests included glucose metabolism, blood lipid levels, and liver and kidney function. The remaining blood samples were stored in a –80℃ refrigerator for further testing. The operators conducting the tests possessed professional qualifications.

#### TCM Syndrome Score

“Pediatrics of Traditional Chinese Medicine” listed a number of TCM symptoms in obesity with gastric-heat and dampness-obstruction syndrome: (1) dizziness and heaviness in the head, (2) thirst, (3) rapid digestion of food and polyorexia, (4) heaviness of limbs, (5) fatigue body and lack of strength, (6) a red tongue, (7) greasy fur, and (8) a slippery pulse. Each item was scored on a scale of 0-2, with 2 points for obvious symptoms, 0 points for nonsymptomatic, and 1 point for symptoms that are between obvious and nonsymptomatic. The total syndrome score was obtained by adding up the scores for each item. A qualified clinician performed the score evaluation.

#### Gut Microbiota Test

Stool samples were collected using Boyou nucleic acid storage tubes (Shanghai Biotechnology Corporation) and stored in a laboratory refrigerator at –80℃. To study intestinal flora diversity, the 16S rDNA target region would be amplified, and information on intestinal microbial diversity and community composition will be obtained by detecting sequence variation and abundance of the target region. The operators possessed professional qualifications.

#### Dietary and Exercise Data

Diet and exercise data were recorded by the children and their families, but they were educated by qualified clinicians before recording [26,27].

(1) **From the baseline to the first month:** The weight of the food was measured using an electronic scale before and after each meal, and photographs were taken as well. Participants were required to wear sports watches every day, including during sleep, but not while bathing, swimming, or in other special cases. Dietary data included the type and weight of the foods consumed, while exercise data included step count, calorie consumption, resting heart rate, sleep duration, and exercise type. All data was meticulously recorded daily in the “Diet and Exercise Handbook.”

(2) **From the second month to the third month:** The method and content remained unchanged. Dietary and exercise data were recorded on Thursdays, Fridays, and Saturdays during 1 week, and distributed at the beginning, middle, and end of the month, rather than every day.

### Participant Timeline

The participant timeline was shown in Table 1, following the Standard Protocol Items: Recommendations for Interventional Trials (SPIRIT) diagram [28].

**Table 1 table1:** Schedule of enrollment, interventions, and assessments for the trial. t1, preinclusion assessment; t0, baseline; t1, intervention for one 1 month; t2, intervention for 3 months.

Time point					Enrolment (–t_1_)		Allocation (t0; Day 0)		Post allocation					Closed out
									*t* _1_ *1 month*		*t* _2_ *3 months*			
**Enrolment**														
			Eligibility screen		✔		N/A^a^		N/A		N/A		N/A	
			Informed consent		✔		N/A		N/A		N/A		N/A	
			Allocation		N/A		✔		N/A		N/A		N/A	
**Interventions**														
		Auricular acupressure		N/A		N/A		✔		✔		N/A		
		Intermittent carbohydrate restriction diet		N/A		N/A		✔		N/A		N/A		
**Assessments**														
	General investigation			N/A		✔		✔		✔		N/A		
	Anthropometry (Height, Weight, WC^b^, and BP^c^)			N/A		✔		✔		✔		N/A		
	Body fat content			N/A		✔		✔		✔		N/A		
	Indexes of liver and renal functions			N/A		✔		✔		✔		N/A		
	Indexes of glucose metabolism			N/A		✔		✔		✔		N/A		
	Levels of serum lipid			N/A		✔		✔		✔		N/A		
	TCM^d^ syndrome score			N/A		✔		✔		✔		N/A		
	Gut microbiota			N/A		✔		✔		N/A		N/A		
	Dietary data			N/A		✔		✔		✔		N/A		
	Exercise data			N/A		✔		✔		✔		N/A		
	Adverse events			N/A		N/A		✔		✔		N/A		

^a^N/A: not applicable.

^b^WC: waist circumference.

^c^BP: blood pressure.

^d^TCM: Traditional Chinese Medicine.

### Sample Size

The primary outcome was the change in body weight from baseline to 1 month. The sample size calculation was based on the difference in weight change between the 2 groups: the TAAT group and the ILCD group.

Our pilot data from 12 patients revealed a weight loss of 1.9 kg after 4 weeks of TAAT and a weight reduction of 1.4 kg after 4 weeks of ILCD, with an SD of 1.1 kg. We assumed a 0.5 kg difference in weight reduction between the 2 arms, power of 0.80, a 2-sided α of .05, and a sample size ratio of 3:1, a minimum sample size of 150 for the TAAT group and 50 for the ILCD group were required, respectively. Assuming a dropout rate of 15%, the trial enrolled at least 240 participants. The “test for 2 means module” of the PASS 16.0 software was used.

### Recruitment

The estimated period for recruitment, intervention, and data collection would take probably 30 months to complete. Eligible clients attending the obesity clinic at the Children’s Hospital of Fudan University were invited to participate in the study through collaboration with TCM clinicians. The time required for participant recruitment and baseline assessment was approximately 30 to 45 minutes.

### Randomization and Blinding

Participants were randomly assigned to either the experimental or control group through a simple randomization process generated by the R Language (version 4.2.2; R core team). This process was designed by the clinical trial unit of the Children’s Hospital of Fudan University and follows a 3:1 allocation ratio.

The study coordinator, who was not involved in data collection, performed the allocation. The randomization list was kept strictly confidential. Allocation was done by the study coordinator in a sequentially numbered fashion using identical, opaque, sealed envelopes. The recruiting clinicians were blinded to study group allocation and did not have access to the allocation sequence.

Eligible participants were enrolled by trained clinicians. The study coordinator independently assigned participants to either the intervention or control groups. Outcome observers were blinded. The analysis team received aggregated data obtained for the control and experimental groups. Study participants could be blinded, but they were scheduled for separate follow-up dates.

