**Methods:**

This is a randomized controlled trial. Eligible participants are children with overweight or obesity and enrolled at the obesity clinic of the department of TCM at a tertiary children’s hospital. Eligible participants must meet the following criteria: (1) be aged between 6 and 18 years, (2) be overweight, and (3) have gastric-heat and dampness-obstruction syndrome. Recruited children will be randomized 3:1 to receive either TAAT or a self-administered ILCD for 1 month: 150 in the TAAT group and 50 in the ILCD group. The primary outcome is the change in body weight from the beginning of treatment to the end of 1 month. Secondary outcomes included body weight, waist circumference, waist-to-height ratio, BMI, blood pressure, body fat content, indexes of liver and renal function, indexes of glucose metabolism, gut microbiota, and TCM syndrome scores at the end of 1 month and 3 months, respectively. Primary statistical analyses were conducted using the intention-to-treat strategy. A generalized linear model was used to compare the difference in weight change between the groups, with the baseline body weight as the covariate, to obtain the estimate of the mean difference in body weight change and its 95% CI, using Gaussian for family function and identity for link function.

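### Simple 3:1 randomisation does not secure the 150:50 minima, and neither the allocation nor the primary model accounts for age or sex in children aged 6 to 18

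*Protocol article*

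**What the plan says.** Under Randomization and Blinding, participants are assigned "through a simple randomization process generated by the R Language", and the process "follows a 3:1 allocation ratio". That section mentions no blocks, strata or minimisation.

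The Abstract (Methods) presents the arm sizes as settled: "150 in the TAAT group and 50 in the ILCD group". The Sample Size section makes the same figures a floor: "a minimum sample size of 150 for the TAAT group and 50 for the ILCD group were required". It then allows for 15% dropout and sets enrolment at 240 or more.

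Analysis of Primary Outcome specifies a Gaussian, identity-link generalized linear model for weight change at 1 month, "with the baseline body weight as the covariate". It names no other covariate. The eligibility criteria admit children from 6 to 18 years of either sex, and define overweight by BMI percentile for sex and age.

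**The concern.** There are two linked issues.

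First, simple randomisation fixes the expected ratio, not the arm sizes. A plan that states a minimum for each arm and then leaves the arm sizes to chance has a mismatch between its sample size and its allocation method. Under 3:1 allocation the smaller arm drives precision, so a low draw for ILCD costs power.

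Second, age and sex are plausible predictors of how many kilograms a child gains or loses in a month. Restricted randomisation could balance them, or the primary model could adjust for them. The protocol does neither, beyond whatever part of their effect baseline weight carries. At stake are some precision and the credibility of the result if the small arm turns out older, younger or different in sex mix.

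**Working it through.** **Inputs.** From Sample Size: difference 0.5 kg ("We assumed a 0.5 kg difference in weight reduction between the 2 arms"), SD 1.1 kg ("with an SD of 1.1 kg"), "a 2-sided α of .05", power 0.80, ratio 3:1, 15% dropout, 240 enrolled. From Randomization and Blinding: simple allocation at 3:1.

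**1. Reproduce the plan's sample size.** Control n = (1.960 + 0.842)² × 1.1² × (1 + 1/3) / 0.5² = 50.7, so 51 ILCD and 153 TAAT, 204 in all. The stated 50 and 150 agree within rounding; power at exactly 150:50 is 79.1% (noncentral t). For dropout, 204/0.85 = 240, which matches the enrolment figure.

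**2. Spread of the ILCD arm.** Under simple 3:1 allocation its size is Binomial(N, 0.25). Power is taken from the noncentral t distribution at the realised split.

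| Children counted | Mean ILCD | 95% range | P(ILCD < 50) | Power at the two ends | Average power | Power at exact 3:1 |
|---|---|---|---|---|---|---|
| 204 (240 less 15%) | 51 | 39–63 | 41% | 71.9%, 84.7% | 79.5% | 79.9% |
| 200 | 50 | 38–62 | 47% | 70.9%, 84.1% | 78.7% | 79.1% |
| 240 (no loss) | 60 | 47–73 | 5.6% | 79.5%, 89.7% | 85.6% | 85.9% |

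The first row matches the plan's own dropout assumption, with the loss taken as equal in both arms. There, power falls below 75% in about 8% of randomisations and below 70% in about 0.8%. Both minima (TAAT at least 150 and ILCD at least 50) are met together only when ILCD lands between 50 and 54, which happens in about 31% of randomisations.

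**3. Chance imbalance in an unadjusted baseline variable.** In SD units, the 95% limit is 1.96 × √(1/150 + 1/50) = 1.96 × 0.163 = 0.32. For sex, assuming half are boys, it is 1.96 × √(0.25 × (1/150 + 1/50)) = 0.16, or 16 percentage points. At 180:60 the limits are 0.29 SD and 15 points.

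**4. What adjustment buys.** A covariate with partial correlation r with weight change, given baseline weight, multiplies the residual SD by √(1 − r²). The documents give no r. Assuming 0.2 to 0.4:

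- r = 0.2: 1 − √0.96 = 2.0% smaller standard error
- r = 0.4: 1 − √0.84 = 8.3% smaller standard error

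**5. Size relative to the existing uncertainty.** At 150:50 the standard error is 1.1 × 0.163 = 0.18 kg and the 95% half-width is 1.96 × 0.18 = 0.35 kg. An imbalance at its 95% limit moves the estimate by r × 0.35 kg, that is 0.07 kg (r = 0.2) to 0.14 kg (r = 0.4). This is part of the 0.35 kg already in the interval, not an error on top of it.

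**The case against.** The case for leaving the plan alone has real weight.

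- **Simple randomisation is legitimate at this size.** It delivers 3:1 on average and costs about 0.4 points of average power. A near-symmetric distribution falls below its mean almost half the time, so the 47% chance of fewer than 50 in 200 is not alarming in itself; at 151:49 power is 78.6%, against 79.1% at 150:50. This stands.
- **Enrolment is 240, not 200.** If all 240 are analysed, ILCD averages 60 and power is 79.5% or better across the 95% range. The primary analysis is by intention to treat, and data from children who withdraw are kept. This stands, so the power concern depends on the 15% loss that the plan itself assumes.
- **Unpredictability has value.** This is one clinic, with treating clinicians who know the allocation. Blocks would make some assignments easier to guess, and 112 children were already enrolled by November 2024. This stands, and is why a mid-trial change of the list is not recommended.
- **Extra covariates can be left to an analysis plan that is not shown.** This stands in part. Omitting age and sex is neither an error nor a contradiction, but the article does state its primary model, and that model can be improved.

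A reader might infer that simple randomisation cannot deliver 150:50, or that an age or sex difference would bias the primary contrast. The documents support neither. The split is attainable but not guaranteed. Chance imbalance under proper randomisation does not bias the estimate on average, and its variability is already in the standard error. Baseline weight probably also carries part of the age and sex signal, though no figure is given for this.

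**Conclusion.** The point holds in a limited form. The allocation method does not secure the per-arm minima that the plan states. On its own dropout assumption, the ILCD arm could plausibly be anywhere from 39 to 63, with power between about 72% and 85%, although the average loss is under one point.

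Age and sex are handled by neither the randomisation nor the stated primary model. The consequence is lost precision and exposure to an unlucky draw, not bias. The 0.32 SD limit follows from the arm sizes alone. The 2 to 8% gain in standard error rests on an assumed partial correlation and would be smaller if baseline weight already captures most of the age effect. This is a modest improvement to a valid design, not a flaw that threatens the trial.

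**What to change.** 1. Before database lock, pre-specify age and sex alongside baseline weight as covariates in the primary Gaussian model. Both are needed to establish eligibility and so are already recorded. The change is one line of analysis text, helps children already allocated as well as those still to come, and costs two degrees of freedom if age enters linearly.
2. In the Abstract and the Sample Size section, describe 150:50 as the split expected under 3:1 allocation, not as fixed arm sizes. This is a wording change only.

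Keep the randomisation list as it is. Switching to blocks part-way would mix two schemes, add some predictability and correct no imbalance already present, for a very small gain in average power.
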